### Procedure

Semistructured phone screening interviews were conducted with individuals who initiated contact via phone or email and remained interested after receiving information about the study. Phone screens were either prescheduled or conducted during the first call of contact, depending on caller preference, and were administered by trained research assistants. Eligible individuals received informed consent forms to sign and return, and were randomized once their signed forms were received at the study site.

Following randomization into the immediate-treatment and waitlist groups, participants in both conditions received a baseline assessment, followed by identical monthly assessments in the ensuing four months. Primary monthly outcomes included suicide ideation (Scale for Suicidal Ideation [33]), severity and frequency of alcohol consumption (Alcohol Use Disorders Identification Test; AUDIT [34], and Self-Administered Web-Based Timeline Followback [35,36]), and emotion dysregulation (Difficulties in Emotion Regulation Scale [37]). Secondary outcome measures included the Reasons for Living Inventory [38], Short Inventory of (Alcohol) Problems (SIP) [39], Patient Health Questionnaire [40], and Dialectical Behavior Therapy - Ways of Coping Checklist [41]. All participants also received brief online weekly assessments on suicide ideation and alcohol consumption. Suicide risk was monitored via weekly assessments.

Prior to treatment, participants also responded to their expectancy of outcome along with the credibility of the intervention (Credibility/Expectancies Questionnaire [42]). At the end of the treatment period, participants reported on their treatment satisfaction (Client Satisfaction Inventory-Short Form [43]) and therapeutic alliance (California Psychotherapeutic Alliance Scale [44]). Participants actively receiving treatment also received brief daily surveys about their urges to quit treatment, use of DBT skills, and engagement level.

All assessments were administered through an online survey platform (Qualtrics [45]) made accessible to participants via Uniform Resource Locator links in scripted emails sent at scheduled timepoints. As compensation for their participation, participants received up to US $120 in Amazon gift cards upon completing each monthly survey (baseline=$15, 4-week=$20, 8-week=$25, 12-week=$30, and 16-week=$30).

### Randomization

Eligible and consenting participants were randomized into the immediate-treatment (n=31) and waitlist groups (n=29). To control for potential covariates that may spuriously affect analytic results, an open source desktop application called MinimPy [46] was used to match participants for equal distribution between conditions on three variables. The three variables were: sex assigned at birth (Demographic Data Schedule), severity of suicide ideation (Suicide Behavior Questionnaire-Revised) and degree of disordered drinking (AUDIT).

### Managing Risk

Suicide risk was carefully monitored in the current study. Participants were assessed at the start and end of the recruitment phone screen, as well as throughout the course of their participation. High risk of suicide during phone-screening was indicated by endorsing 4 or more points on a 7-point Likert scale, or an increase of 3 or more points from the start of screening on urge to die by suicide. Throughout the 16-week trial period, weekly questionnaires assessing suicide risk were emailed to all participants. These emails included prompts on: (1) frequency of suicidal urges in the past week, (2) intensity of suicidal urges in the past week, (3) seriousness of acting out on suicidal urges in the past week, and (4) current suicidal urge, all using 5-point Likert scales. Participants endorsing a rating of 3 or higher on any item, or a 2-point increase from the previous week, would be called by phone and assessed for suicide risk. Additionally, the number for the National Suicide Prevention Lifeline was situated next to prompts on suicidality received by all participants.

The principal investigator was on call to intervene by phone at any time. Evidence-based procedures based on the University of Washington Risk Assessment Protocol (UWRAP) [47] were implemented by the principal investigator whenever further assessments of risk were warranted. The UWRAP guides the assessor through a suicide risk assessment procedure that evaluates the presence of a plan, access to means, likelihood of following through with a plan, being interrupted by others, et cetera. If a participant was determined to be at high risk based on this interview and the clinical judgment of the principal investigator, a safety plan was to be developed with the cooperation of the participant and the principal investigator. If a participant was unavailable by phone, a nonjudgmental *caring email* (see Multimedia Appendix 2) was sent, which expressed concern and encouraged participants to reach out to a suicide hotline or textline provided in the email.

### Intervention

One primary aim of iDBT-ST is to replace maladaptive behavioral strategies with alternative strategies for coping and emotion regulation. The current intervention comprises the skill-training component alone, which is administered in a computerized format. The intervention was modified from an online DBT skills training intervention for emotion dysregulation [48].

Participants randomized into the iDBT-ST group were immediately enrolled into the online treatment program, and received weekly sessions over a period of 8 weeks. After completing the eighth session, participants in active treatment were transitioned into a follow-up phase that entailed monthly and weekly assessments without treatment. Participants randomized into the waitlist group received repeated monthly assessments as well as weekly surveys for 8 weeks prior to receiving treatment.

The iDBT-ST intervention was administered through an online electronic learning server (Articulate Online [49]) which consists of 8 sessions (Table 1) accessible through an access portal individualized for each participant, with one new session activated each week. The sessions begin with a weekly assessment, followed by (1) a review of the last session at weeks 2-8, (2) an introduction of the current session, (3) skills teaching, and (4) summary and consolidation. The skills were taught via videos and graphics describing the skills and examples, along with interactive activities. The intervention completion rate of each participant was also monitored through the server. If consented by participants, reminders to complete sessions were sent via their preferred method before the next session became available. Individualized assignments of skill practice were provided following the completion of each session. See Figure 1, Figure 2, and Figure 3 for screenshots of the intervention.

**Table 1 table1:** Description and function of session contents.

Session	DBT module	Skills	Function
1	Mindfulness	Observing, Describing, Participating	To introduce the foundational skills to develop nonjudgmental awareness of the present
2	Mindfulness	Nonjudgmentally, One-Mindfully, Effectively	To teach how to practice mindfulness with skillful effectiveness
3	Addiction	Dialectical Drinking, Clear Mind	To help learners find a middle path between oppressive sobriety and unrestrained freedom of drinking, and develop a clear mind
4	Addiction	Community Reinforcement, Burning Bridges	To teach strategies to identify relationships and activities that aim to stop or reduce problematic drinking
5	Emotions Regulation	Understanding Emotions	To teach the functions of emotions, and how to describe them
6	Emotions Regulation	Handling Unwanted Emotions	To teach skills to reduce frequency and quantity of unwanted emotions
7	Emotions Regulation	Building Mastery and Copy Ahead	To teach skills to build future resilience against intense emotion
8	Distress Tolerance	TIP (Temperature of face, intense exercise, paced breathing), Distract	To teach skills that help weather crises and intense negative emotions

Sessions 3 and 4 were designed to target problematic drinking, and included the new skill *Dialectical Drinking*. The skill of dialectical drinking describes the abstinence violation effect (see Figure 4), goal setting, pros and cons of maintaining or changing their drinking behavior, as well as an assessment of motivation and confidence to follow-through on their drinking goal. Dialectical drinking incorporates aspects of motivational interviewing [50] and harm reduction [51] as ways to nonjudgmentally reinforce a change toward goal-oriented drinking behavior. Problematic drinking is also targeted through the DBT skills of *Community Reinforcement*, whereby participants identify people, activities, and places that can reinforce their drinking goal, as well as *Burning Bridges*, whereby participants eliminate people, activities, and places that would reinforce their problematic drinking. In burning bridges, participants learned a variety of methods to manage alcohol cravings [15,16]. See Table 2 for common alcohol reduction strategies and their DBT counterparts.

**Table 2 table2:** DBT skills that target problematic drinking.

Alcohol Reduction Strategy		Skill
**Deciding to make a change**		
	Goal setting	Dialectical Drinking
	Decisional balance	Dialectical Drinking
	Assessment of motivation and interest	Dialectical Drinking
	Abstinence violation effect	Dialectical Drinking and Clear Mind
	Tracking behavior	Daily diary card
**Making a change**		
	Contingency management	Contingency Management and Burning Bridges
	Craving management	Burning Bridges
	Drink refusal strategies	Dialectical Drinking

**Figure 1 figure1:**
[figure not shown]
Screenshot of the session overview.

**Figure 2 figure2:**
[figure not shown]
Screenshot of interactive activity (selecting drinking goal).

**Figure 3 figure3:**
[figure not shown]
Screenshot of interactive activity (changing emotions).

**Figure 4 figure4:**
[figure not shown]
New Dialectical Behavioral Therapy skill: dialectical drinking.

**Figure 5 figure5:**
[figure not shown]
CONSORT diagram. DERS: Difficulties in Emotion Regulation Scale; iDBT: Internet-delivered Dialectical Behavioral Therapy; ITT: intention-to-treat.

### Confidentiality

All information provided by participants will be strictly confidential. Answers to phone screens and online assessments that will be kept indefinitely for research purposes were coded in a nonidentifying way, and stored in password-protected files on an encrypted server accessible only to the principle investigator and trained research assistants. Confidential records linking participant names with their respective research identification number will be deleted no later than September 30^th^, 2018. All identifying information from ineligible individuals was deleted immediately after phone screening. Additionally, the study site is a secure research clinic equipped with noise-cancelling devices to prevent conversations with participants from being overheard. Voice messages left for participants were devoid of details about the study and other sensitive information that may compromise confidentiality. Any paper documents that contained confidential Patient Health Information are kept in a locked area in the study site where access is restricted, and will be shredded before disposal. These documents may be examined in strictly confidential checks conducted by government or university staff for legal and safety insurance.

Participants were informed of one scenario in which confidentially may be breached. That is, if a participant reveals an imminent high risk of danger to their own or someone else’s life, research staff may address that risk to police or emergency resources.

### Power Calculation

A power analysis was not conducted because the primary purpose of the data analyses is to describe the effect of iDBT-ST protocol treatment over time using repeated observation data in a preliminary manner. The results will be used to help determine if further research on the treatment program for suicidal heavy drinkers is necessary in larger samples.

### Analyses

Intervention effects will be evaluated by examining change outcomes as a function of treatment condition using both hierarchical linear modeling (HLM) [52] for outcomes with a normal distribution and generalized estimating equations (GEEs) [53,54] for count outcomes. Both HLM and GEEs accommodate observations that are missing at random, thus increasing the power of analyses. Analyses will be conducted using an intent-to-treat framework, in which all randomized and available participants will be included in the analyses. To examine changes over time for the entire sample, analyses will be conducted among all participants during all assessment waves (baseline to 16-week). A set of analyses will also be conducted using the first three assessment waves (baseline to 8-week) comparing immediate-treatment to no treatment, and at each condition’s relative pretreatment, midtreatment (4-week for iDBT-ST; 12-week for waitlist), and posttreatment (8-week for iDBT-ST; 16-week for waitlist) assessment phases.

Given the pilot nature of the study, all outcomes will be evaluated in terms of effect sizes as well as clinically significant change using Jacobson and Truax’s specifications [55]. Treatment effect sizes will be analyzed using Cohen’s *d* and Relative risk ratios for continuous and count outcomes, respectively. Cohen’s *d* will calculate within-condition effect sizes across all assessment waves. Descriptive analyses will also be conducted to examine acceptability.

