### Participants

Participants were recruited from ads placed online (eg, Craigslist, Reddit) and in a local newspaper containing a brief description of the study. Interested participants were phone screened for eligibility on alcohol use severity, frequency of binge drinking episodes, suicidal ideation, emotion dysregulation, mental health treatment history, and demographic characteristics. Inclusion criteria included: (1) being 18 years or older, (2) endorsing suicidal ideation in the past month (defined as endorsing a wish to die at least once in the past 30 days), (3) engaging in at least two episodes of heavy drinking in the past month, (4) high emotion dysregulation (defined as scoring one standard deviation above the normative mean on the 16-item Difficulties in Emotion Regulation Scale [32]), and (5) residing in the United States. Exclusion criteria included: (1) currently receiving psychotherapy; (2) diagnosis of bipolar I, schizophrenia, or schizoaffective disorder; (3) non-English speaking; (4) unable to read or write; and (5) having no access to a computer connected to the Internet. Of 398 individuals who expressed initial interest, 60 of 91 eligible individuals returned the informed consent forms and were randomized into the immediate-treatment (n=31) and waitlist (n=29) groups. One person randomized to the immediate-treatment group did not complete any of the assessments, leaving 59 people included in the analyses. The phone screening process helped us prevent participants from enrolling with multiple identities.

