## Results

Recruitment to the study began June 17, 2016 and ended September 14, 2016. Data were collected using direct entry of online surveys tools (Qualtrics [45], Articulate Online [49]) by February 2017, and are currently undergoing analyses. The CONSORT diagram (Figure 5) presents the flow of participants during recruitment, enrollment, and participation. Of the 398 individuals who expressed interest in participating, 91 were determined to be eligible through the screening process. A total of 60 individuals returned their informed consent and were randomized, of whom 59 individuals were intended-to-treat. A total of 50 participants in the study were retained through the 16-week enrollment.

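### The missing-at-random claim holds for the likelihood-based models but not in general for GEE, the method named for count outcomes

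*Protocol article*

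**What the plan says.** The Analyses section of the protocol article assigns HLM to normally distributed outcomes and "generalized estimating equations (GEEs) [53,54] for count outcomes". It then makes one statement on missing data, covering both methods: "Both HLM and GEEs accommodate observations that are missing at random, thus increasing the power of analyses". The analysis set is defined by availability: "Analyses will be conducted using an intent-to-treat framework, in which all randomized and available participants will be included in the analyses". Effects are to be reported as follows: "Treatment effect sizes will be analyzed using Cohen’s *d* and Relative risk ratios for continuous and count outcomes, respectively". The comparison of randomized arms is made "using the first three assessment waves (baseline to 8-week) comparing immediate-treatment to no treatment"; other analyses use all waves to week 16.

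On loss, participants were "randomized into the immediate-treatment (n=31) and waitlist (n=29) groups". One person in the immediate-treatment group completed no assessment, which leaves 59 for analysis (Participants). The Results section adds: "A total of 50 participants in the study were retained through the 16-week enrollment". The Discussion says waitlist retention in particular had been expected to be difficult. It gives no loss by arm.

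The Procedure section lists AUDIT and the Timeline Followback as primary alcohol measures. The article does not say which outcomes are treated as counts. Drinking frequency from the Timeline Followback is the likeliest candidate, by inference.

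**The concern.** The sentence puts HLM and GEE on the same footing under missing at random (MAR), where dropout may depend on outcomes already observed. A correctly specified likelihood model remains valid there. GEE solves an estimating equation whose terms average to zero only if, given the modelled covariates, being observed is unrelated to the outcome residual. If people with a high earlier count are more likely to leave, that fails. Only special cases escape, and how far the estimate moves depends on the working correlation. This is a property stated wrongly, not a detail left for an analysis plan to supply.

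At stake are the rate ratios for count outcomes, probably including a primary drinking measure. If heavier drinkers leave the waitlist, the remaining waitlist mean falls and a real reduction looks smaller; if lighter drinkers leave, the error runs the other way. The Power Calculation section says the results will help decide whether larger studies are needed, so a distorted effect size would enter that decision.

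**Working it through.** **1. The plan's own figure.** Retention is 50/60 = 83.3%, as the Discussion states. The person with no assessments is outside the analysed set, so among those analysed it is 50/59 = 84.7%, and loss is 9/59 = 15.3% by week 16. The article gives no power, alpha or effect size to reproduce.

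**2. Simulation matched to that loss.** All inputs other than the loss are assumptions.
- Three waves (baseline, 4 and 8 weeks), Poisson counts, baseline mean 20, between-person log-SD 0.8, and autocorrelated wave noise (SD 0.5, correlation 0.7).
- Log-mean falls by 0.15 per wave in both arms and by a further 0.15 per wave under treatment. The true week-8 rate ratio is exp(−2 × 0.15) = exp(−0.30) = 0.741.
- Dropout per wave averages 1 − √(1 − 0.153) = 8.0%. Its logit depends only on the last observed count (log scale, slope 1.5 unless stated), so it is MAR by construction.
- Samples of 8,000 to 12,000 over 8 or 12 runs, to separate bias from noise. The weighted GEE uses the true retention probabilities.

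Week-8 rate ratio (truth 0.741):

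| Dropout pattern | Full data | GEE, independence | GEE, exchangeable | Weighted GEE |
|---|---|---|---|---|
| Unrelated to drinking | 0.737 | 0.738 | 0.737 | 0.738 |
| Same dependence in both arms | 0.741 | 0.751 | 0.761 | 0.719 |
| Waitlist only, slope 0.75 | 0.739 | 0.825 | 0.736 | 0.740 |
| Waitlist only, slope 1.5 (two sets of runs) | 0.738, 0.743 | 0.922, 0.934 | 0.742, 0.747 | 0.729, 0.749 |
| Opposite dependence by arm | 0.744 | 0.982 | 0.729 | 0.745 |

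Monte Carlo standard errors on the log scale are 0.004 to 0.012, except 0.031 for the 0.719.

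**3. A second simulation with other assumptions** (40,000 people, baseline mean 8, log-SD 0.8, true ratio about 0.70).
- Waitlist dropout driven by the previous count, 29% against 6% missing at week 8: independence 0.97, exchangeable 0.72, truth 0.69.
- Opposite predictors by arm, 18% against 21% missing: 0.95 and 0.70.
- One common mechanism: 0.71 to 0.72 against 0.70.

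**4. Size against sampling error.** With 59 participants, a null simulation under assumed inputs gave an SD of 0.249 for the log rate ratio. Around 0.70, the 95% range from chance alone is 0.70 × exp(±1.96 × 0.249) = 0.43 to 1.14. The exchangeable bias in step 3 is ln(0.72/0.69)/0.249 = 0.043/0.249 = 0.17 SD. The independence bias is ln(0.97/0.69)/0.249 = 0.341/0.249 = 1.37 SD.

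**The case against.** The strongest reply is that the sentence says the methods accommodate incomplete records and so gain power, which is about keeping cases and makes no claim of unbiasedness. This stands in part. A reader might infer that the plan declares bias impossible; it does not. But the sentence names the MAR mechanism, and it is the article's only missing-data provision for an analysis of available data, so the wording cannot rest on the milder meaning alone.

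A reader might also infer that the drinking results are biased, and by a large amount. The documents do not support that:
- No link between dropout and drinking is reported. Expecting waitlist retention to be hard does not show that loss differed by arm, and loss that depends on arm alone does no harm when arm is modelled.
- The large shifts need both an independence working correlation and mechanisms that differ by arm. The article fixes no working correlation, which is fair to leave to a fuller document.
- The simulated losses are on the high side. In step 3, 29% of 29 plus 6% of 30 is about 10 people gone by week 8, and 18% of 29 plus 21% of 30 is between 11 and 12, against 9 over the full 16 weeks. Step 2 also puts the whole 16-week loss into the first 8 weeks. Intermittent missed assessments could add to the week-8 figure, but these simulations model dropout.
- That the affected outcome is a primary one is inferred.

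Finally, a reader might infer that the confidence intervals will be too narrow. In one simulation at n = 59 (1,500 replicates), the ordinary sandwich test rejected 7.7% of the time at nominal 5%, and a bias-reduced version 6.7%. These figures come from that single simulation and were not independently checked. The article names neither a variance estimator nor an alpha, so no error in the document is shown.

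**Conclusion.** The statement is wrong for standard unweighted GEE and should be corrected. With 15.3% of the analysed participants lost, the consequence ranges from negligible to large. Under the assumed inputs of step 2 (truth 0.741), the ratio stays at 0.73 to 0.76 with an exchangeable correlation and at about 0.75 with independence and a common mechanism. It moves to 0.83 to 0.98 with independence and arm-specific mechanisms. Exchangeable correlation is helpful but no guarantee: the 0.761 under a common mechanism differs from 0.741 by 0.027 on the log scale, with a Monte Carlo standard error of 0.005.

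The conclusion that bias is possible rests on GEE being unweighted and on dropout depending on earlier counts; the article establishes neither. For a proof-of-concept pilot with preliminary, descriptive aims, this is a minor to moderate point, not one that must be fixed before the trial's results can be used.

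**What to change.** Limit the MAR sentence to likelihood-based models. Analyse count outcomes with a Poisson or negative-binomial mixed model with a random intercept and fixed effects for wave, condition and condition-by-wave. With a log link and a random intercept of common variance, averaging over the intercept multiplies every mean by the same factor, so the rate ratios are already population-average and need no further conversion. The MAR validity depends on correct model specification; this model was not part of the simulations, and the case for it rests on likelihood theory.

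If GEE is kept, either impute multiply from earlier outcomes first, or state that it relies on MCAR or covariate-dependent missingness, use a non-independence working correlation and add a sensitivity analysis. Inverse-probability weighting worked in the simulations, but with known retention probabilities and thousands of participants; here a dropout model would rest on about 9 losses. A small-sample variance correction is an optional extra.

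The cost is one corrected sentence and a changed model specification, with no new data. The Results section reports that analysis was still under way.

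### The treatment effect size for continuous outcomes is specified only as a within-condition Cohen's d, which can overstate the intervention's effect; no standardised effect is defined from the planned between-condition comparison

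*Protocol article*

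**What the plan says.** All of the following is in the Analyses section of the protocol article unless another section is named.

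- Effect sizes are one of two named yardsticks: "all outcomes will be evaluated in terms of effect sizes as well as clinically significant change".
- Treatment effect sizes are to be expressed as Cohen's d "and Relative risk ratios for continuous and count outcomes, respectively".
- The next sentence says which d: it "will calculate within-condition effect sizes across all assessment waves". No other d is described.
- The section opens with a controlled analysis: "Intervention effects will be evaluated by examining change outcomes as a function of treatment condition", by hierarchical linear models (HLM) or generalized estimating equations (GEE). One set of analyses uses the first three waves ("baseline to 8-week) comparing immediate-treatment to no treatment").
- Entry required high emotion dysregulation, "scoring one standard deviation above the normative mean on the 16-item Difficulties in Emotion Regulation Scale" (Participants). It also required a recent wish to die and recent heavy drinking.
- The waitlist waited 8 weeks and was then treated (Intervention).
- On use: "The results will be used to help determine if further research on the treatment program" is needed in larger samples (Power Calculation). The opening of Methods adds that the project is to inform a full-scale randomised trial.

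**The concern.** A treatment effect size should estimate what the treatment adds. Pre-post change inside one arm cannot do so, because it also counts every other cause of change. This design has several. People were admitted because they scored high or had recent episodes, so some decline is expected without treatment. Both arms also received monthly batteries, weekly surveys and telephone calls triggered by reported risk, and any benefit of that contact would be credited to the intervention.

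The trial randomised an untreated comparison group for 8 weeks, which is what is needed to remove these influences. The d that the article specifies does not use it. At stake is the number that readers, and the designers of the next trial, are most likely to lift from the report. If a within-arm d were taken as the effect that a two-arm trial must detect, that trial would be too small.

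**Working it through.** The article states no effect size, power or sample-size target, so there is no figure to reproduce. The inputs from the article are the entry cutoff (+1 SD), the numbers analysed (30 and 29) and the 8-week controlled window. Everything marked *assumed* below is not in the article.

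**1. What each quantity estimates.** Let δ be the standardised treatment effect over weeks 0–8 and c the standardised change that would occur anyway, with a common baseline SD.

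- Within-arm d, immediate treatment, weeks 0–8: δ + c
- Within-arm d, waitlist, weeks 0–8: c
- Between-condition d, weeks 0–8: (δ + c) − c = δ

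Only the last is a treatment effect.

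**2. How large c could be from selection alone.** *Assumed:* source scores are normal with mean μ and SD 1 in normative units; entry means a score above +1; r₁ is the correlation of screening score with baseline and r₂ with week 8. Let λ be the selected group's mean excess over μ, and v its variance. Then

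c = (r₁ − r₂) λ / √(1 − r₁²(1 − v)).

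Screening precedes baseline, so regression that is complete by baseline is not counted.

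| Source mean μ | λ | v | r₁/r₂ = 0.80/0.75 | 0.85/0.70 | 0.90/0.60 |
|---|---|---|---|---|---|
| 0 | 1.525 | 0.199 | 0.11 | 0.35 | 0.77 |
| +1 SD | 0.798 | 0.363 | 0.05 | 0.16 | 0.34 |
| +1.5 SD | 0.509 | 0.486 | 0.03 | 0.10 | 0.20 |

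Example, μ = 0 and 0.85/0.70: 0.15 × 1.525 = 0.229; √(1 − 0.7225 × 0.801) = 0.649; 0.229/0.649 = 0.35. If r₁ = r₂, c is 0. Natural recovery and assessment effects would come on top.

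**3. What this would do to a sample size, if d were used for one.** n per arm = 2(1.96 + 0.8416)²/d² (80% power, two-sided 5%). Power with 25 per arm = Φ(d/√(2/25) − 1.96). *Assumed:* an observed within-arm d of 0.80, which gives 2 × 7.849/0.64 = 24.5, so 25 per arm.

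| c | Between-condition d | n per arm needed | Power with 25 per arm |
|---|---|---|---|
| 0 | 0.80 | 25 | 81% |
| 0.10 | 0.70 | 33 | 70% |
| 0.35 | 0.45 | 78 | 36% |

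**4. Precision of a between-condition d in this pilot.**

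- Unadjusted, complete data: 1.96 × √(1/30 + 1/29) = 0.51.
- Baseline-adjusted, *assumed* baseline to week-8 correlation 0.6: 0.51 × √(1 − 0.36) = 0.41.
- Missing data widen both. With 25 per arm (*assumed*; the article gives only 50 retained to week 16), the unadjusted figure is 1.96 × √(2/25) = 0.55.

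**The case against.** The strongest reply is that the controlled comparison is already in the plan. The Analyses section models outcomes by condition and compares immediate treatment with no treatment from baseline to week 8. A reader might infer from the d sentence that the randomised control is thrown away; that is not so. The gap is narrower: no standardised effect is defined from that comparison, and the d that is defined carries the treatment label.

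Second, a reader might infer that the next trial will be under-sized. The article does not support this: it nowhere says that d will enter a sample-size calculation. The risk is that d can mislead, not that it will.

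Third, it is tempting to say that the waitlist's d pools 8 untreated with 8 treated weeks. The wording may equally mean a d at each wave, and the section elsewhere aligns assessments to each arm's own treatment phases. The text is ambiguous on this.

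Fourth, within-condition d has a legitimate use. The Introduction's fourth aim includes change over time in the comparison group, and a waitlist d over weeks 0–8 would display much of the non-specific change. That supports keeping it as description. It does not make the immediate arm's d a treatment effect.

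Fifth, the illustration is soft. Respondents to advertisements who also report suicidal ideation and heavy drinking may come from a population already above the norm, and then selection produces less regression. The lower rows of the first table show this.

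A journal article may leave the exact standardiser to a fuller plan. But the choice of a within-condition d is stated, so it is not a matter of omitted detail.

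**Conclusion.** The point holds in limited form. For continuous outcomes, the quantity labelled as the treatment effect size is specified only within condition and cannot separate the intervention from regression to the mean, natural recovery or assessment effects. It can therefore overstate the effect in a pilot meant to inform a full-scale trial. The planned baseline-to-week-8 comparison supplies a controlled estimate, so the defect lies in which number is standardised and labelled, not in the whole analysis.

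No single figure for the inflation can be defended. The range of 0.03 to 0.77 rests on assumed correlations, an assumed source mean and normality, and the 78 v 25 per arm contrast is one cell of that grid combined with an assumed observed d of 0.80. The direction is what matters. The point does not extend to count outcomes: the article does not say whether the relative risk ratios are within or between conditions.

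**What to change.** State in the Analyses section that the treatment effect size for continuous outcomes is the between-condition difference at week 8, either baseline-adjusted or taken as the baseline-to-8-week HLM contrast, divided by the pooled baseline SD and reported with its 95% confidence interval. Use that estimate and its interval, rather than a within-arm d, wherever the pilot's effect informs the next trial.

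Keep within-condition d, labelled as descriptive. For the waitlist, report weeks 0–8 (untreated) separately from weeks 8–16 (treated), which also settles the ambiguity about waves.

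The cost is a sentence or two and a few lines of code. No new data are needed, and the Results section says that analysis was still under way. The downside is that the headline effect sizes will probably be smaller and their intervals wide: at an unadjusted between-condition d of 0.5 with complete data, SE = √(1/30 + 1/29 + 0.25/118) = 0.26, giving about −0.02 to 1.02.
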